### Randomization

First- and second-stage treatment assignments are conducted by a designated member of the study team at each site using the minimization method [62, 63], a modified, adaptive randomization procedure that ensures treatment conditions are balanced in regard to pre-treatment stratification variables. This method accommodates many stratification variables by weighting each equally and seeks to achieve an overall balance of the levels of these variables across experimental conditions, rather than a balance within each stratum. The variables used in randomization include age (< 55 vs. ≥ 55 years), sex (male vs. female), insomnia severity (ISI scores < 15 vs. ≥ 15), pre-PAP AHI (≥ 20 and < 20), and objective PAP adherence (> 4 h vs. ≤ 4 h per night determined by PAP download data for the 30 days prior to study entry). Randomization is performed independently at each site by one designated study staff via a computer-based Fortran program developed by the study statistician, and all study coordinators are blinded to participant randomization.

### Data management and analysis

Plots of the longitudinal outcome variables will be created to examine trends over time. Additionally, all variables will be tested to determine if parametric distributional assumptions are valid. The hypothesis tests listed below describe parametric models for binary or continuous outcomes. Linear (mixed or standard) models will be used for the latter and can also be applied to integer-valued outcomes that have a sufficient number of potential values, for which a normal approximation is adequate. For simplicity, the term “continuous outcomes” will be utilized. For continuous outcomes that are not approximately normally distributed or cannot be suitably transformed, nonparametric analyses will be conducted. Socio-demographic, psychiatric, medical, and sleep characteristics will first be described using central tendency and dispersion indices for continuous variables, as well as frequency distributions for nominal data. Characteristics of participants in different treatment arms will be compared with basic statistical tests to verify that the randomization worked as anticipated. For longitudinal models, all available records from participants will be used in analyses, including those who drop out of the study. Characteristics of dropouts will be compared with completers and methods of correction will be employed in final models if deemed necessary (i.e., multiple imputation or inverse probability weighting) [64]. Methods to account for potential missing-not-at-random (MNAR) data will also be applied as a sensitivity analysis [65].

## Aim 1: To test OCBT-I augmentation of usual PAP care (UC) as a first-stage intervention

We hypothesize that insomnia remission rates after the first stage of treatment will be higher for individuals in the OCBT-I intervention group than the UC group. To test this hypothesis, a mixed effects logistic regression will be utilized, with remission (Y/N) as the outcome and treatment group, time, site, and the group-time-site interaction as predictors. Treatment group by time will be the predictor variable. Follow-up sensitivity analyses will include covariates, such as participant demographics. Separate logistic regression models will be conducted for the secondary sleep apnea and insomnia outcome indicators. Similarly, mixed effects linear regression models will be employed for continuous sleep outcome measures, such as sleep duration, efficiency, and PAP adherence.

Power calculations for aim 1 were completed based on two independent proportion tests using a z-approximation due to the larger sample sizes. Previous work [32] suggests that approximately 50% of OCBT-I recipients reach remission, compared to approximately 15% of those in the control group. However, considering the comorbid sample and the somewhat rigorous remission definition of the current study, conservatively powered estimates were utilized for detecting a difference between 35% (OCBT-I) and 15% (UC). Factoring in an attrition rate of 15% and using a 5% alpha value, 96% power was projected to detect this difference between groups, with 82 UC and 245 OCBT-I subjects. The lowest the remission rate in the OCBT-I group can be in order to retain at least 80% power is 30.2%.

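### The primary Aim 1 model leaves out the five factors used to minimise allocation; the test stays valid but is less efficient than it could be at no cost

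*Protocol article*

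**What the plan says.** All locations are in the protocol article.

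- **Randomization.** First- and second-stage assignments both use minimisation. The factors are age (cut at 55), sex, "insomnia severity (ISI scores < 15 vs. ≥ 15), pre-PAP AHI (≥ 20 and < 20), and objective PAP adherence". PAP adherence is "determined by PAP download data for the 30 days prior to study entry"; the section gives no such date for ISI. Site is handled by separate runs: "Randomization is performed independently at each site by one designated study staff".
- **Aim 1.** The mixed-effects logistic model for remission has "treatment group, time, site, and the group-time-site interaction as predictors". On anything further the section says: "Follow-up sensitivity analyses will include covariates, such as participant demographics". ISI, AHI and PAP adherence are not named there as covariates.
- **Table 1 and Primary outcome measures.** Entry requires ISI of 10 or more; remission is ISI below 8.
- **Aim 2.** Continuous outcomes get linear mixed models over all time points; binary outcomes get generalised linear models at each time point. The listed mixed-model predictors are group, time, group by time, and site with its interactions.

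**The concern.** Minimising on prognostic factors makes the arms more alike than simple randomisation would, so the treatment estimate varies less from trial to trial. A model that omits those factors computes its standard error as if that balance had not been imposed. The test then tends to reject too rarely under the null and loses power under the alternative.

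The article makes a stated choice here, so the matter is not simply left to an analysis plan that is not shown. One allocation factor (site) is in the primary model, five are out, and covariates are assigned to sensitivity analyses. The investigators thought baseline ISI relevant enough to balance on, yet it has no route into the primary model. What is at stake is efficiency and calibration of the primary test, not bias in favour of treatment.

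**Working it through.** **1. The plan's own power figure.** Inputs from Aim 1: 82 UC and 245 OCBT-I evaluable (96 × 0.85 = 81.6; 288 × 0.85 = 244.8), rates 15% and 35%, alpha 5% (taken as two-sided), two-proportion z-test.

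- Pooled rate: (82 × 0.15 + 245 × 0.35)/327 = 98.05/327 = 0.2999.
- Null SE: √[0.2999 × 0.7001 × (1/82 + 1/245)] = 0.0585.
- Alternative SE: √[0.15 × 0.85/82 + 0.35 × 0.65/245] = 0.0498.
- Power: Φ[(0.20 − 1.96 × 0.0585)/0.0498] = Φ(1.71) = 95.7%. The stated 96% is reproduced.
- At 30.2% the same formula gives Φ[(0.152 − 1.96 × 0.0562)/0.0491] = Φ(0.85) = 80.2%. The stated limit is reproduced.

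**2. Can baseline severity enter through the repeated outcome?** If the qualifying ISI is the baseline record, every baseline ISI is at least 10. The baseline value of the remission indicator is then non-remission for everyone. A constant carries no information about who started at 11 and who started at 24. The Abstract's different remission cut-off (below 10) would not change this.

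**3. What adjustment would gain.** The documents give no prognostic strength, so it is assumed as a range. The settings were:

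- 327 participants, two sites, and 3:1 minimisation within site on the five binary factors.
- Assumed factor prevalences of 50%, 40%, 70%, 50% and 60%.
- An assumed biased coin: probability of OCBT-I 0.95, 0.75 or 0.15, according to whether that assignment would improve, not affect or worsen balance.
- 2,500 trials per scenario, each analysed by logistic regression at the end of stage 1 with group + site, and again with the five factors added.

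The SD of the covariate linear predictor was about 0.3, 0.6 or 1.0. By SD²/(SD² + 3.29) these are latent R² of about 0.03, 0.10 and 0.23.

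| Scenario (unadjusted → adjusted) | SD 0.3 | SD 0.6 | SD 1.0 |
|---|---|---|---|
| Power, 35% vs 15% | 95.9 → 96.4% | 96.0 → 96.9% | 96.1 → 97.8% |
| Power, 30.2% vs 15% | 79.6 → 80.4% | 79.7 → 82.8% | 81.9 → 87.9% |
| Type I error, both 25% | 4.5 → 4.9% | 4.3 → 5.0% | 2.9 → 4.8% |
| Type I error, both 15% | 4.7 → 4.8% | 4.7 → 5.4% | 3.1 → 4.4% |

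Simulation error is about 0.4 points for type I error and for power near 96%, and about 0.8 points for power near 80%. The gain is therefore about 0 to 2 points at the planned effect and about 1 to 6 points at the 30.2% limit. The unadjusted test is clearly conservative only in the strong case.

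**4. Stage 2.** Aim 2 expects 140 evaluable OCBT-I non-remitters; split 1:1, that is 140/2 = 70 per arm. In the linear mixed models, week-8 values are among the repeated outcomes, so they are already in the analysis. The binary models at each time point have no such link, and no week-8 covariate is named for them. No stage-2 simulation was run, so no size is claimed for this part.

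**The case against.** The strongest reply is that little is lost. The trial is planned at 96% power, and the 30.2% rate is the edge of the design, not its target. With weak factors the gain is about the size of simulation error. A covariate-adjusted analysis is already planned, and its demographic example is illustrative, so it could include all five factors. The simulation also simplifies the planned model (no random effect, no time or interaction terms) and assumes a minimisation probability that the article does not state. All of this stands and limits the size of the point. It does not give a reason to keep the less efficient analysis as primary.

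Two stronger readings are tempting and not supported:

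- A reader might infer that the primary test is invalid or that substantial power is being wasted. The error is in the conservative direction, and at the planned effect the difference is at most about 2 points over the assumed range.
- A reader might infer that week-8 ISI and week-8 PAP adherence are both unbalanced and unadjusted throughout stage 2. Randomization dates only PAP adherence to before study entry; whether ISI is updated for the second assignment is not stated. The linear mixed models already use week-8 values of continuous outcomes.

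**Conclusion.** The point holds as an efficiency and calibration weakness. The primary Aim 1 model omits the five factors on which allocation is minimised, and the binary outcome cannot supply baseline severity. The test remains valid, with type I error at or below about 5%, falling to about 3% only if the factors are strongly prognostic. The power gain from adjustment is about 0 to 2 points at 35% vs 15% and about 1 to 6 points at 30.2% vs 15%.

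These sizes rest on the assumed prognostic strength, factor prevalences and minimisation probability, and on a single-time-point logistic model in place of the planned mixed model. The plan's stated power figures are correct. For stage 2 the point is confined to the binary models at each time point.

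**What to change.** - **Aim 1:** put the five minimisation factors in the primary model together with site, using ISI, age, AHI and PAP adherence as continuous variables where they were measured so. Keep the unadjusted model as the sensitivity analysis.
- **Effect measure:** report a standardised (marginal) risk difference. Adjusted and unadjusted odds ratios estimate different quantities, so moving between the models would otherwise change the estimand as well as the precision.
- **Stage 2:** in the binary models for the re-randomised comparison, also adjust for week-8 ISI and week-8 PAP adherence. State which ISI measurement the second-stage minimisation uses.

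The cost is analysis wording, to be fixed before outcomes are examined by arm. The baseline factors are already recorded for allocation. The Procedures section repeats the baseline measures after the first 8 weeks, and the OSA outcomes section tracks PAP adherence at each assessment. At the planned rates about 98 remissions are expected by the end of stage 1 (12.3 + 85.75), or about 14 for each of the seven coefficients for group, site and the five factors at that time point.

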## Methods

### Study design and setting

This study is employing a Sequential Multiple Assignment Randomized Trial (SMART) design to test value added of providing a therapist-directed CBT-I as a second stage treatment to those who do not initially achieve acceptable outcomes with OCBT-I. Eligible patients are being randomly assigned in a 3:1 ratio to an online (OCBT-I) program (Sleepio^TM^) combined with usual PAP care or to a usual PAP care (UC) only condition. All eligible patients receive sleep hygiene education at their baseline assessment. Eight weeks after randomization, patients randomized to OCBT-I who meet study criteria for remission, defined as a score of less than 8 on the Insomnia Severity Index [37], will receive no further insomnia treatment and those who do not meet remission criteria are randomized again in a 1:1 ratio to a 2nd-stage intervention consisting of either therapist-lead CBT-I (TCBT-I) or continued, extended access to the OCBT-I resources. All participants complete all study outcome measures at baseline and several time points post-randomizations (8 weeks, 16 weeks, 3 months, and 6 months; see Figs. 1 and 2). Those assigned to the UC condition are offered CBT-I (choosing either OCBT-I or TCBT-I) at the end of the study period.

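### As described, the Aim 1 linear mixed models for continuous outcomes compare change from baseline, which is valid but less precise than adjusting for baseline

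*Protocol article*

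**What the plan says.** Under the Aim 1 heading, the protocol article describes a mixed logistic model for remission with "treatment group, time, site, and the group-time-site interaction as predictors". It then names the term of interest: "Treatment group by time will be the predictor variable". Covariates are placed outside the main model: "Follow-up sensitivity analyses will include covariates, such as participant demographics".

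For continuous outcomes the same section says: "Similarly, mixed effects linear regression models will be employed for continuous sleep outcome measures, such as sleep duration, efficiency, and PAP adherence". It gives no separate list of terms, so the opening word of that sentence carries over the preceding specification. The Aim 2 section describes the same structure for its mixed models: group, time, group by time, and site with its interactions.

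Study design and setting confirms that baseline values are available: "All participants complete all study outcome measures at baseline and several time points post-randomizations", the later points being 8 weeks, 16 weeks, 3 months and 6 months. Nowhere does the article enter the baseline value of the outcome as a covariate or set the arms equal at baseline. The Randomization section adds that allocation is minimised on five factors, among them dichotomised PAP use before entry.

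**The concern.** Aim 1 concerns the effect after the first stage, and the full set of measures is repeated once in that stage, at week 8. A group-by-time term then exists only if baseline is one of the levels of time, that is, if the baseline value is a row of the outcome. With a free group main effect, the model estimates a separate baseline mean for each arm, and the group-by-time coefficient is the difference between arms in mean change.

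Randomisation makes the expected baseline means equal, so estimating a baseline difference adds only noise. The change score subtracts the whole of any chance baseline difference, where the efficient correction subtracts only the part that predicts the week-8 value. Minimisation on PAP use limits chance imbalance for that outcome, but the standard error of the unconstrained model does not use this.

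At stake is the width of the confidence intervals for sleep time, sleep efficiency, PAP adherence and the other continuous secondary outcomes. The usual-care arm has only 82 evaluable participants, and no power is stated for any continuous outcome.

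**Working it through.** **Inputs from the document (Aim 1 section).** 245 OCBT-I and 82 UC evaluable participants (288 and 96 less 15% attrition: 244.8 and 81.6); remission 35% versus 15%; alpha 5%, taken as two-sided.

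**Assumptions, not in the document.** Rho is the correlation between baseline and week 8. k is the baseline SD divided by the week-8 SD. Effects are in units of the week-8 SD. Site is ignored.

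**1. The plan's own figure.** Pooled proportion = (82 × 0.15 + 245 × 0.35)/327 = 0.300. SE under the null = sqrt(0.300 × 0.700 × (1/245 + 1/82)) = 0.0585. SE under the alternative = sqrt(0.1275/82 + 0.2275/245) = 0.0498. Power = Phi((0.20 - 1.96 × 0.0585)/0.0498) = 95.7%. The stated 96% reproduces. It concerns the binary outcome and does not depend on the point made here.

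**2. The tested term is a change-score contrast.** In a simulated two-time-point data set with 245 and 82 participants, a random-intercept model with group, time and group by time gave a group-by-time coefficient of 0.4367. The raw difference in mean change was also 0.4367. Dropping the group main effect cut the variance of the coefficient to 0.751 of its value (rho 0.5).

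**3. Variance per person, equal SDs (k = 1).**
- Change from baseline: 2(1 - rho)
- Baseline adjusted, or baseline means constrained equal: 1 - rho²
- Ratio, adjusted to change: (1 + rho)/2, so the loss is (1 - rho)/2

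| rho | change | adjusted | information lost | adjusted power when power as written is 80% |
|---|---|---|---|---|
| 0.3 | 1.40 | 0.91 | 35% | 94% |
| 0.5 | 1.00 | 0.75 | 25% | 90% |
| 0.7 | 0.60 | 0.51 | 15% | 86% |
| 0.8 | 0.40 | 0.36 | 10% | 84% |

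Simulation (4,000 runs per value) gave variance ratios of 0.65, 0.73 and 0.86 at rho 0.3, 0.5 and 0.7, against 0.65, 0.75 and 0.85 from the formula. Below rho 0.5 the change score has variance above 1, so it is less precise than the week-8 value alone.

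**4. At the planned sizes, rho 0.5, k = 1.** sqrt(1/245 + 1/82) = 0.1276.
- SE as written: 0.1276 × sqrt(1.00) = 0.128 SD
- SE adjusted: 0.1276 × sqrt(0.75) = 0.111 SD
- Effect detectable with 80% power: 2.80 × 0.1276 = 0.36 SD as written, 2.80 × 0.1105 = 0.31 SD adjusted
- Power for an assumed effect of 0.30 SD: 65% as written, 78% adjusted

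**5. Unequal SDs.** The change-score variance becomes 1 + k² - 2k·rho; the adjusted variance stays at 1 - rho². At rho 0.5:
- k = 0.8: 1 + 0.64 - 0.80 = 0.84; ratio 0.75/0.84 = 0.89; loss 11%; 80% power rises to about 84%
- k = 0.7: 1 + 0.49 - 0.70 = 0.79; ratio 0.75/0.79 = 0.95; loss 5%; 80% power rises to about 82%

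**The case against.** **The specification is partly inferred.** The sentence on continuous outcomes lists no terms, and the article never says outright that baseline is a level of time. The remission template cannot be carried over literally either: entry requires an ISI of at least 10 and remission is an ISI below 8, so nobody can be in remission at baseline. How baseline enters could be settled in a full protocol or analysis plan that is not shown. This stands as a limit on certainty. It does not remove the point, because the article does name the terms and the tested interaction, puts covariates only in sensitivity analyses, and offers no other specification for Aim 1.

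**There may be more than two time points.** The diary and actigraphy schedule is in a figure that is not shown. If treatment-stage records enter with time as a continuous variable, the formulas above do not apply. If time is categorical and data are complete, the week-8 minus baseline contrast is still a difference in mean change.

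**Equal SDs may not hold.** Eligibility requires sleep onset latency or wake time after sleep onset above 30 minutes on three or more nights per week, which may narrow the baseline spread of the sleep outcomes. Step 5 of the working shows that the loss is then smaller. PAP adherence is not truncated in this way, since varying levels of adherence are admitted.

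**Importance.** These are secondary outcomes, and the only hypothesis spelled out in the Aim 1 section is remission. The 80% starting power is therefore only a reference point.

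**Stronger readings that a reader might infer.** One is that the planned analysis is biased or invalid. It is not: under randomisation the change-score contrast is unbiased and its test is valid. Another is that a fixed quarter of the information is lost. That figure belongs to rho 0.5 with equal SDs, neither of which the document gives, and it may differ between diary, actigraphy and PAP outcomes.

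**Conclusion.** The point holds as a matter of precision on the continuous secondary outcomes. On the plain reading of the Aim 1 section, the linear mixed models test a difference in change from baseline, and a model that uses the randomised equality of the arms at baseline estimates the same effect with a smaller standard error. With equal SDs the loss of information about the treatment effect is 35% to 10% for rho from 0.3 to 0.8. At rho 0.5 it falls to about 5 to 11% if the baseline SD is 0.7 to 0.8 of the week-8 SD. The result rests on baseline and week 8 being the first-stage time points and on the terms being carried over from the remission model. The primary outcome and its power are not affected. Because the gain costs almost nothing, the change is worth making before analysis.

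**What to change.** For all continuous Aim 1 outcomes, state in the analysis section or analysis plan that:

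- the arms share a common baseline mean within site, so the treatment main effect and any group-by-site term at baseline are dropped;
- time, site and group by post-baseline time are kept, and any planned site interaction applies only to the post-baseline treatment effect;
- the covariance over time is unstructured, so that baseline and week-8 SDs may differ;
- the reported result is the week-8 OCBT-I minus UC difference with its 95% CI.

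A week-8 analysis of covariance on the baseline value is a close alternative. It is not fully equivalent, because it drops participants who miss either value unless these are imputed, whereas the constrained mixed model keeps everyone with at least one of them.

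The cost is a change of wording before analysis. It needs no new data, visits or participants.

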## Aim 2: To determine the value of the first to second stage CBT-I (OCBT-I or TCBT-I) stepped care model relative to UC for improving insomnia and OSA outcomes after 2nd stage treatment and at 3- and 6-month follow-up

We predict that among participants who did not achieve insomnia remission during the first intervention stage, those assigned to the stepped care TCBT-I group will have the best outcomes. Specifically, we hypothesize that the OCBT-I to TCBT-I group will show significantly greater improvements in insomnia and OSA outcomes compared to the OCBT-I to extended OCBT-I group and compared to non-remitters in the UC group at the end of phase 2 and at follow-up time points (3- and 6-month). To test this hypothesis, linear mixed models (continuous outcomes) across all time points will be utilized, followed by generalized linear models (binary outcomes) at each specific time point. The mixed effects models will include treatment group, time, and group by time predictors, as well as site and its interaction with the other predictors. In order to account for the adaptive nature of the study design in which some subjects receive two treatment modalities and some only one, weighting of records will be employed based on inverse probability weighting (IPW) principles [66].

Power calculations for aim 2 included several considerations. Specifically, based on findings from a previous sequential insomnia treatment study, a second stage of treatment is thought to enhance response rates by about 20% [67]. For the current study, we predict that 5% (UC) and 20% (OCBT-I) of participants will remit after the second stage time frame. If aim 1 expectations are correct, approximately 85% of the 96 UC subjects (*n* = 82) and 65% of the 288 OCBT-I subjects (*n* = 187) will be non-remitters. Further allowing for a 25% attrition by the end of stage 2, these non-responder sample sizes would be 61 (UC) and 140 (OCBT-I). These expected remission percentages and sample sizes yield 83% power to detect differences between groups using an alpha of 5%, based on a 2-proportion *z*-test. Even with IPW methods utilized for adjustment, these calculations suggest adequate power for the comparison.

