### Objectives and design rationale

The main objective of this study is to determine if augmentation of usual care PAP therapy with online CBT-I (OCBT-I) improves insomnia and OSA outcomes, as well as to determine the added benefit of providing a higher intensity, second stage, therapist-led CBT-I (TCBT-I) to patients who demonstrate sub-optimal short-term outcomes with OCBT-I. Specifically, the study aims include:Aim 1: To test OCBT-I augmentation of usual PAP care (UC) as a first-stage intervention in patients with comorbid OSA/insomniaAim 2: To determine the value of the first to second stage CBT (OCBT-I or TCBT-I) stepped care model relative to UC for improving insomnia and OSA outcomes after second stage treatment and at 3- and 6-month follow-upExploratory aim: To determine if second stage TCBT-I produces significantly greater short and longer-term improvements in insomnia and OSA outcomes than second stage OCBT-IExploratory aim: To examine pre-treatment relationships between syndrome-specific OSA and insomnia symptoms and to determine how these relationships are modified by treatment and influence global sleep-related outcomes

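### Aim 2 asks whether the whole stepped-care model beats UC, but its stated UC contrast and power cover only week-8 non-remitters, a comparison that randomisation does not protect

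*Protocol article*

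**What the plan says.** In Objectives and design rationale, Aim 2 is: "To determine the value of the first to second stage CBT (OCBT-I or TCBT-I) stepped care model relative to UC". The heading of the Aim 2 analysis section repeats this.

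The hypothesis under that heading is narrower. It applies "among participants who did not achieve insomnia remission during the first intervention stage" and makes two comparisons for the OCBT-I to TCBT-I group. One is with OCBT-I to extended OCBT-I. The other is with UC participants who also failed to remit: "compared to non-remitters in the UC group at the end of phase 2 and at follow-up time points". The power paragraph follows the same restriction: "these non-responder sample sizes would be 61 (UC) and 140 (OCBT-I".

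On the design, Study design and setting says of the OCBT-I arm that "those who do not meet remission criteria are randomized again in a 1:1 ratio to a 2nd-stage intervention". No second randomisation is described for UC. The Aim 1 power paragraph expects the first randomisation to change week-8 remission, since it plans for "detecting a difference between 35% (OCBT-I) and 15% (UC". On adjustment, Aim 2 says that "weighting of records will be employed based on inverse probability weighting (IPW) principles", because some participants receive two treatment modalities and some only one. Study design and setting also states that everyone completes all outcome measures at every time point.

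**The concern.** Whether a participant is a week-8 non-remitter is decided after randomisation and, by the plan's own expectation, is affected by the arm. Restricting both arms to non-remitters removes 35% of OCBT-I and 15% of UC. The remaining 65% and 85% are selected to different degrees, so the groups need not be alike in prognosis, and no second randomisation restores the balance for UC.

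The restriction also changes the question. A stepped-care model works partly by getting people well at the first step. Leaving these people out, together with any relapse among them, means that the contrast is not the effect of the model named in the aim. Nor is it a clean effect of the second step, because any lasting effect of first-stage OCBT-I is still present in the OCBT-I non-remitters. A positive or a null result would be hard to read as an answer to Aim 2.

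**Working it through.** **1. Reproduce the stated power.** Inputs from the Aim 2 power paragraph: 96 UC and 288 OCBT-I; non-remission 85% and 65%; attrition 25%; stage-2 remission 5% and 20%; alpha 5%, taken as two-sided.

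- Non-remitters: 0.85 × 96 = 81.6 (82); 0.65 × 288 = 187.2 (187). After attrition: 0.75 × 82 = 61.5 (61 in the plan); 0.75 × 187 = 140.25 (140).
- Power = Φ[(|p1 − p2| − 1.96·s0)/s1], with s0 the pooled and s1 the unpooled standard error. Here s0 = 0.0554 and s1 = 0.0438, so (0.15 − 0.1087)/0.0438 = 0.943 and power = 82.7%.

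This matches the stated 83%, so the non-remitter restriction is what the trial was powered on, not loose wording.

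**2. Who is left out.** 0.35 × 288 ≈ 101 OCBT-I and 0.15 × 96 ≈ 14 UC participants. If remitters stay remitted, the plan's rates give at week 16:

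- Stepped care: 0.35 + 0.65 × 0.20 = 48%.
- UC: 0.15 + 0.85 × 0.05 = 19.25%.

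Of the 28.75-point difference, 35 − 15 = 20 points arise in stage 1 and 13 − 4.25 = 8.75 points in stage 2.

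**3. Size of the selection (illustrative).** Assume week-8 and week-16 ISI are bivariate normal with correlation ρ, a fixed remission threshold, week-8 remission of 15% and 35%, and a second stage that does nothing. The thresholds in SD units are t0 = Φ⁻¹(0.15) = −1.036 and t1 = Φ⁻¹(0.35) = −0.385, so the SD itself does not matter. The week-16 remission rates in week-8 non-remitters are:

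- UC: P(Y < t0 | X > t0)
- OCBT-I, stage-1 effect gone: P(Y < t0 | X > t1)
- OCBT-I, stage-1 effect persisting: P(Y < t1 | X > t1)

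| ρ | UC | OCBT-I, effect gone | Selection alone | OCBT-I, effect persisting | Observed difference |
|---|---|---|---|---|---|
| 0.4 | 11.9% | 9.2% | −2.6 | 26.1% | +14.2 |
| 0.6 | 9.7% | 6.0% | −3.8 | 21.0% | +11.2 |
| 0.8 | 6.9% | 2.4% | −4.5 | 14.6% | +7.7 |

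Differences are in percentage points, from unrounded rates. The model is not calibrated to the plan's 5% for UC non-remitters. A second model that is (a normal prognostic factor with the same log-odds slope on both stages; slopes 0.5, 1 and 2) gives OCBT-I non-remitters 4.8%, 4.2% and 3.0% against 5% when stage 2 does nothing. The direction is the same and the shift smaller.

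**4. The all-randomised contrast.** With 25% attrition in both arms, n = 0.75 × 288 = 216 and 0.75 × 96 = 72. The plan's 20% is assumed for both second-stage options.

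- Whole arm, same pooled formula: s0 = 0.0669, s1 = 0.0576, power 99.7%.
- One regime, weights 1 and 2: 75.6 remitters and 70.2 non-remitters. Effective n = (75.6 + 2 × 70.2)²/(75.6 + 4 × 70.2) = 216²/356.4 = 130.9; pooled formula 99.0%.
- One regime, weighted variance: (1/216){0.35·E[(Y − p)² | remitter] + 0.65·2·E[(Y − p)² | non-remitter]} = 0.4046/216 = 0.00187. Adding UC, 0.1925 × 0.8075/72 = 0.00216, gives SE 0.0635 and power 99.5%.
- Assumed 40% relapse of remitters in both arms: 0.35 × 0.6 + 0.13 = 34% versus 0.15 × 0.6 + 0.0425 = 13.25%. Power for one regime is 91.9% (effective n) or 95.7% (weighted variance).

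The document gives no relapse rate.

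**The case against.** Several points can fairly be made for the plan.

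- **Part of the hypothesis is sound.** TCBT-I versus extended OCBT-I among OCBT-I non-remitters rests on the 1:1 re-randomisation. This stands in full. Aim 1 is also untouched.
- **The weighting may imply that remitters are in the model.** Design weights are of little use if only non-remitters are analysed, and the mixed models run across all time points. Exclusion of remitters from the fitted model is therefore inferred, not stated. This stands as an ambiguity, but the hypothesis and the power calculation both name non-remitters, and no contrast of all randomised participants with UC is described.
- **The weights might handle the selection.** The weight model is not given, so this cannot be ruled out for every form of weighting. Weights from the known re-randomisation probabilities cannot do it. They are constant among OCBT-I non-remitters, and UC has no second randomisation to weight by.
- **A carried-over stage-1 effect belongs to the sequence.** The contrast with UC concerns OCBT-I followed by TCBT-I, so a lasting OCBT-I benefit is a real effect of that sequence. This also stands.

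Because of the last point, a reader might infer from the table that the design manufactures up to 14 points of false benefit. It does not show that. In the persisting case the true effect in those same OCBT-I non-remitters is about 17, 15 and 12 points, and selection pulls the observed difference below it.

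**Conclusion.** The stated objective and the stated UC contrast do not match. The aim is the whole stepped-care model against UC. The contrast is between two subsets defined by an outcome of the first randomisation, with the stage-1 remitters left out of the hypothesis and the power. That conclusion needs no modelling.

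The size does. In the latent-normal model, selection alone costs stepped care about 2.6 to 4.5 points, against a planned difference of 15. A persisting stage-1 effect can outweigh this and make the net difference positive. The correlations are assumptions, and another model gives smaller shifts, so neither size nor direction can be taken as established.

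Two further inferences should be resisted. It would be wrong to say that Aim 2 as a whole is invalid, since its comparison of second-stage treatments is randomised. It would also be wrong to read about 99% against 83% as a straight gain in power: the two figures concern different estimands (28.75 and 15 points), and the 99% assumes that no remitter relapses. What can be said is that the all-randomised contrast is well powered on the plan's own rates, and still about 92 to 96% per regime at an assumed 40% relapse.

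**What to change.** Make the main Aim 2 comparison with UC the two embedded regimes, in all randomised participants, for remission at week 16 and at the 3- and 6-month follow-ups:

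- OCBT-I, then TCBT-I if unremitted, versus UC;
- OCBT-I, then extended OCBT-I if unremitted, versus UC.

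Use weight 1 for OCBT-I remitters (who contribute to both regimes), 2 for re-randomised non-remitters and 1 for UC, with robust standard errors clustered on participant. State explicitly that remitters are in this model.

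Keep the non-remitter analysis for TCBT-I versus extended OCBT-I. Label the contrast with UC non-remitters as descriptive.

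Restate the power for the new contrast, with the assumed relapse rate shown. The figures above are per contrast at two-sided 5%, without adjustment for having two regimes.

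The cost is a change of wording and a little more programming. No new data are needed, because remitters and all UC participants are assessed at every visit. The change should be fixed before the Aim 2 analysis is run.
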